## 5.0 STUDY HYPOTHESES

The primary implementation hypothesis is that the system-level multicomponent package of implementation strategies for oncology symptom assessment and management at NMHC will increase the cluster-level reach rate of cPRO to eligible patients. The primary effectiveness hypothesis is that cancer patients at NMHC who are randomized to EC will have better PRO outcomes over time compared to cancer patients at NMHC who are randomized to UC.

Secondary implementation hypotheses are that the system-level multicomponent package of implementation strategies for oncology symptom assessment and management at NMHC will increase adoption of cPRO at the provider level as evidenced by referrals for appropriate services when a patient triggers in cPRO and the reach rate of patients enrolling in the portal. It is also hypothesized that system-level strategies will be appropriate, acceptable, feasible, and sustainable. Secondary effectiveness hypotheses are that cancer patients at NMHC who are randomized to EC will have lower healthcare utilization, better cancer treatment delivery, better cancer treatment satisfaction, better health related quality of life, better self-management, lower toxicity, better physical health and lower financial burden compared to cancer patients at NMHC who are randomized to UC.

The exploratory hypothesis is that cancer patients randomized to EC will have better clinical outcomes compared to cancer patients randomized to UC.

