### Effectiveness

Target enrollment in the patient-randomized trial comparing EC v. UC in the post-I phase is approximately 1000 patients. The target enrollment for the patient-randomized component of the trial was based on planned longitudinal modeling of monthly evaluations of 5 PROs for anxiety, depression, fatigue, physical functioning and pain interference. Assuming a compound symmetry covariance structure for the longitudinal measurements with within-subject correlations of 0.5 at all time points, a sample size of 360 is required to achieve 90% power to achieve statistical significance at a Bonferroni-corrected  $p < 0.01$  for an anticipated average difference of 0.3 SD across all time points for EC v. UC. An overall recruitment goal of  $n=1000$  was set to accommodate dropout of up to 64% of patients over time. A Bonferroni correction was used for a conservative estimate of required sample size; for statistical analyses the more powerful step-down Dunnett procedure will be used for p-value adjustment. It is also noted that the target sample size of  $n=1000$  also provides greater than 90% power for detecting a 0.3 SD difference in the FACT G-7 (evaluated at 5 time points) under similar covariance assumptions as the other PROs, as well as simple change-from-baseline differences in PROs from 0 to 12 months using linear models.

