## 9.0 STATISTICAL ANALYSES - EFFECTIVENESS

### 9.1 Primary Outcomes - Effectiveness

#### PROs

Using each of the separate PROMIS domain status scores (i.e., Anxiety, Depression, Fatigue, Pain Interference, and Physical Function) collected at baseline and at regular monthly intervals, primary analyses will use longitudinal models to estimate the time-averaged difference in PROs across groups. Primary effectiveness estimates will be based on post-I data with a comparison of longitudinal PROs for patients randomized to Post-I EC v. Post-I UC. Linear mixed models will be used for these analyses with a fixed effect for treatment arm (Post-I EC v. Post-I UC) as the primary predictor of interest and fixed effects for model adjustments for cluster, cancer continuum, gender, language preference, baseline PRO value and time of enrollment (categorical variable for quarter enrolled). Individual-level random effects with an autoregressive covariance structure will be included in the mixed models to account for dependence of within-individual PRO measurements over time. Multiple comparisons adjustment for the five primary tests of hypothesis will be performed using the step-down Dunnett procedure. For reporting purposes, confidence intervals for treatment effects for the five primary outcomes will be reported with lower and upper bounds simultaneously estimated to correspond with Dunnett correction. Sensitivity of model estimates and statistical inference under unstructured and compound symmetry covariance structures will be explored. In addition to the overall time-averaged difference, we will also report estimated differences from baseline at specific monthly timepoints.

Secondary analyses will also examine changes from baseline to the 12-month follow-up time point as well as change from baseline to the other monthly follow-up time points using the directly observed differences from baseline at these timepoints. Linear regression will be used for these analyses with treatment arm (Post-I EC v. Post-I UC) as the primary predictor of interest and model adjustments for cluster, cancer continuum, gender, language preference, baseline PRO value and time of enrollment (categorical variable for quarter enrolled). These effect estimates will be compared to effect estimates at each time point calculated in the primary analysis model that uses all longitudinal measurements.

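### Step-down Dunnett, a several-groups-versus-one-control method, is applied to five endpoints in a two-arm comparison, so the adjusted p-values and simultaneous intervals rest on the wrong reference distribution

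*Combined protocol and SAP*

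**What the plan says.** SAP 6.0 (Effectiveness) sizes the randomized comparison with a Bonferroni level: "a sample size of 360 is required to achieve 90% power to achieve statistical significance at a Bonferroni-corrected" threshold of 0.01, for a time-averaged difference of 0.3 SD. It then changes method for the analysis: "for statistical analyses the more powerful step-down Dunnett procedure will be used for p-value adjustment". SAP 9.1 repeats this ("Multiple comparisons adjustment for the five primary tests of hypothesis will be performed using the step-down Dunnett procedure") and adds that confidence intervals for the five outcomes will be simultaneous and correspond to the Dunnett correction. By their titles, two of the sources cited for the procedure and its intervals (SAP References 5 and 6) concern comparison of several processes with a standard and comparison with a control.

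On the model, SAP 6.0 plans with this covariance: "Assuming a compound symmetry covariance structure for the longitudinal measurements with within-subject correlations of 0.5 at all time points". SAP 9.1 specifies: "Individual-level random effects with an autoregressive covariance structure will be included in the mixed models", with unstructured and compound symmetry as sensitivity analyses. The listed fixed effects are arm, cluster, cancer continuum, gender, language, baseline score and quarter of enrollment. The same section promises "effect estimates at each time point calculated in the primary analysis model that uses all longitudinal measurements".

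**The concern.** Dunnett's procedure needs several contrasts against one control. Their correlation then follows from the group sizes: with equal groups, each contrast has variance 2σ²/n and each pair shares the control's σ²/n, giving 0.5. In this trial there are two randomized arms and one contrast per endpoint. What links the five test statistics is the correlation among anxiety, depression, fatigue, pain interference and physical function. The SAP neither states that correlation nor says how to obtain it from five separate mixed models. Two analysts could follow the text and report different adjusted p-values for the primary effectiveness claims.

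The model text has two further gaps. Without month and arm-by-month terms, one arm coefficient gives one constant effect, not twelve monthly ones. And the covariance sentence can be read in more than one way, with different consequences for the standard error.

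**Working it through.** **Inputs from the documents.** SAP 6.0: five endpoints, 0.3 SD, constant correlation 0.5, 0.01 per test, 90% power, N = 360, up to 64% dropout, goal 1000. SAP 2.0: baseline plus 12 monthly measures, so m = 12. SAP 3.0: 1:1 allocation.

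**Assumptions.** The endpoint correlation r is not given, so a range of 0 to 0.8 is shown, equal for all pairs. Tests are two-sided, with normal limits.

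**1. The plan's own figure.** Variance of the 12-month mean under compound symmetry: (1 + 11 × 0.5)/12 = 0.5417 SD². Per arm: n = 2(2.576 + 1.282)² × 0.5417/0.3² = 2 × 14.88 × 0.5417/0.09 = 179.1, so 180 per arm and 360 in total. This reproduces. One-sided 0.01 would give 314, so the plan used two-sided tests. 360/(1 − 0.64) = 1000 also reproduces. The implied family-wise level is 5 × 0.01 = 5%; neither SAP 6.0 nor 9.1 writes it.

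**2. Critical values, two-sided, by number of hypotheses remaining.**

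| Remaining | 5 | 4 | 3 | 2 | 1 |
|---|---|---|---|---|---|
| Step-down Dunnett (0.5) | 2.51 | 2.44 | 2.35 | 2.21 | 1.96 |
| Holm | 2.58 | 2.50 | 2.39 | 2.24 | 1.96 |

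The first Dunnett step corresponds to p = 0.0120 instead of 0.01.

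**3. Family-wise error when 2.51 is applied to five endpoint statistics, all nulls true.** With equal correlation r,
FWER = 1 − ∫ φ(u) [Φ((c − √r·u)/√(1−r)) − Φ((−c − √r·u)/√(1−r))]⁵ du.

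| r | Dunnett, c = 2.51 | Bonferroni/Holm | c that gives 5% |
|---|---|---|---|
| 0 | 5.9% | 4.9% | 2.57 |
| 0.3 | 5.6% | 4.7% | 2.55 |
| 0.5 | 5.0% | 4.2% | 2.51 |
| 0.7 | 4.1% | 3.5% | 2.44 |
| 0.8 | 3.5% | 3.0% | 2.37 |

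Check at r = 0: 1 − (1 − 0.0120)⁵ = 5.9%. With two to four true nulls the error is at most 5.7%. Under any dependence the first step is bounded by 5 × 0.0120 = 6.0%.

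**4. Power cost of Holm's first step.** At 180 per arm the standardized effect is 0.3/√(2 × 0.5417/180) = 3.867. Power for one endpoint is Φ(3.867 − 2.576) = 90.2% at Holm's first threshold and Φ(3.867 − 2.511) = 91.2% at Dunnett's.

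**5. Covariance, taking SAP 6.0's constant 0.5 as true.**

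- *AR(1) alone, model-based standard errors.* The fitted parameter is 0.5. Model variance of the time average: (1 + 0.5)/(12 − 10 × 0.5) = 0.2143. The estimator weights the first and last months 1 and the others 0.5, so its actual variance is 0.5 + 0.5 × (4.5/49) = 0.5459. SE ratio: √(0.2143/0.5459) = 0.63. A nominal 5% test then runs at 2[1 − Φ(1.960 × 0.627)] = 22%, and a nominal 1% test at about 11%. Adjusting for baseline turns the correlation of 0.5 into (0.5 − 0.25)/(1 − 0.25) = 0.333, and the ratio is again 0.63.
- *Random intercept plus AR(1) residual.* Compound symmetry is nested (AR parameter zero). SE ratio 1.00, no inflation.
- *AR-structured random effects plus independent residual.* The fitted autocorrelation goes to 1. SE ratio 1.00, no inflation.

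**6. Fixed effects.** None of the listed terms indexes follow-up month; quarter of enrollment is calendar time. The listed model therefore cannot produce the monthly effects promised from it.

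**The case against.** The strongest reply is that little is lost in practice. The excess over 5% is under one percentage point, it arises only if the endpoint correlation is below 0.5, and above that the method is conservative. The SAP never says that 0.5 will be used. A step-down test using the true endpoint correlation would be valid: in simulation it gave 4.9% to 5.6% (4000 runs, Monte Carlo SE about 0.35 points). All of that stands, and it limits the size of the point. It does not repair the text, which names a procedure whose reference distribution does not fit the tests and supplies nothing in its place. The three-group model in SAP 9.1 (EC, UC, Pre-I, with UC as referent) does have a shared control, but the SAP attaches Dunnett to the five primary tests, not to that model.

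On covariance, a reader might infer that the primary tests will run at 22%, or that unstructured covariance must be made primary. The documents support neither. The 22% requires AR(1) with no random effect, and SAP 9.1 names individual-level random effects. Planning under one structure and analyzing under another is not in itself an error in alpha. Unstructured and compound symmetry are already planned as sensitivity analyses, so promoting one of them would be a preference.

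On the monthly effects, time terms are evidently intended. The gap is one of wording and has not been shown to distort the primary arm test.

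**Conclusion.** The multiplicity method does not match the family of tests and should be replaced. Family-wise error under the textbook version is 5.9%, 5.0% or 3.5% at endpoint correlations of 0, 0.5 or 0.8: slightly anti-conservative or conservative, depending on a quantity that the SAP does not give. This rests on equal correlations, normal limits and two-sided tests. A reader might go further and infer that a stated 5% level is broken. That is not supported, because no such level is written and the direction of any departure is unknown.

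The missing month and arm-by-month terms are a real but smaller inconsistency. The covariance wording needs one clarifying sentence: it affects the standard error only if AR(1) is fitted alone with model-based standard errors.

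**What to change.** In SAP 6.0 and 9.1:

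- Replace step-down Dunnett with Holm, or with a step-down max-T that uses the estimated correlation of the five arm contrasts, and say how that correlation is obtained across the five models.
- Use intervals matched to the chosen test. Alternatively, report 99% Bonferroni intervals and label them conservative and not exactly matched to Holm, whose last step rejects at p < 0.05, where a 99% interval can still include zero.
- State the family-wise alpha and sidedness. The hypothesis in SAP 5.0 is directional ("randomized to EC will have better PRO outcomes over time compared to cancer patients at NMHC who are randomized to UC"), while N = 360 reproduces only with two-sided tests.
- Add categorical follow-up month and arm-by-month terms, and define the primary effect as the equal-weight mean of the monthly EC v. UC contrasts.
- State that the autoregressive structure is fitted together with a random intercept, or use robust standard errors.

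The cost is SAP wording; SAP 1.0 says such changes need no protocol amendment. Stated power is unaffected because N = 360 was computed at 0.01. The downside is a slightly larger first-step critical value under Holm (2.58 v. 2.51), about one point of power for a single endpoint at 180 per arm.

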#### Primary effectiveness outcomes in NU IMPACT:

- Individual-level PROMIS measures collected at baseline and monthly up until 12 months after enrollment
  - PROMIS Anxiety v1.0
  - PROMIS Depression v1.0
  - PROMIS Fatigue v1.0
  - PROMIS Pain Interference v1.1
  - PROMIS Physical Function v1.2

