## Effectiveness Study

A schematic of the study design that illustrates the effectiveness investigation is depicted in Figure 2. For the last 6 months of each cluster's pre-I phase, eligible participants are invited to consent to monthly administration of a collection of PRO surveys administered through REDCap for one year following consent. One set of comprehensive PRO surveys will be administered at baseline and monthly thereafter, and an additional set of questionnaires will be included with these PRO surveys on a quarterly basis (see Section 2.0 for primary and secondary effectiveness PROs and timing). During post-I, EC becomes available using a 1:1 randomization scheme (EC:UC) to new, consenting patients, but not those in the consented group from the pre-I period who are continuing their care. Randomization will be stratified by cluster, cancer continuum (curative, non-curative, survivorship), gender and language preference. Participants who consent to randomization during post-I will receive the REDCap PRO surveys on the same schedule as those who consented during the pre-I phase. The monthly PRO data collected over one year of follow-up during the post-I embedded patient-randomized trial will be the primary data source for the effectiveness analysis. Additionally, we will compare the post-I EC and UC arms to patients enrolled during pre-I. Pre-I patients will have access to identical tools as UC patients, and the comparison of these arms will be critical for noting potential contamination in provider care subsequent to system-wide implementation strategies.

| Clinical Cluster | Implementation Phase | Y3                         |                            |                              |                              | Y4                                                    |                                                       |                                                       |                                                       | Y5                                                    |                                                       |                                                       |    | Y6 |    |    |    |

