|------------------|----------------------|----------------------------|----------------------------|------------------------------|------------------------------|-------------------------------------------------------|-------------------------------------------------------|-------------------------------------------------------|-------------------------------------------------------|-------------------------------------------------------|-------------------------------------------------------|-------------------------------------------------------|----|----|----|----|----|
|                  |                      | Q1                         | Q2                         | Q3                           | Q4                           | Q1                                                    | Q2                                                    | Q3                                                    | Q4                                                    | Q1                                                    | Q2                                                    | Q3                                                    | Q4 | Q1 | Q2 | Q3 | Q4 |
| Cluster 1        | PRE                  | Non-Randomized Recruitment |                            | Pre-I: Follow-up Only        |                              |                                                       |                                                       |                                                       |                                                       |                                                       |                                                       |                                                       |    |    |    |    |    |
|                  | POST                 |                            |                            | Randomized Trial Recruitment |                              | UC - Follow-up Only
EC - Follow-Up & Enhanced Care |                                                       |                                                       |                                                       |                                                       |                                                       |                                                       |    |    |    |    |    |

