Recognizing the possibility of contamination effects for the treatment arms during the post-I period, we will augment the primary analyses to include longitudinal PRO data from the Pre-I period. Linear mixed models will be used as described for the primary analyses but extending the primary predictor of interest to a multicategory variable (Post-I EC, Post-I UC, Pre-I). Adjustments for cluster, cancer continuum, gender, language preference, baseline PRO value and time of enrollment, and the individual-level random effects, will be included as described above. The Post-I UC cohort will be treated as the referent group to facilitate formal primary comparison with outcomes for the Post-I EC group, and to gauge comparability of outcomes for Post-I UC and Pre-I patients. This approach will also allow for a contrast test between Post-I EC and Pre-I. If longitudinal PROs for Post-I UC and Pre-I are not significantly different, and if the effectiveness estimate for Post-I EC v. Pre-I is similar to the primary Post-I EC v. Post-I UC comparison, this will suggest lack of contamination. If longitudinal PRO differences for Post-I UC v. Pre-I are significantly different and/or the effectiveness estimate for Post-I EC v. Pre-I is different from the primary Post-I EC v. Post-I UC comparison, this may suggest some level of treatment arm contamination during the Post-I phase. This latter scenario may also be indicative of system-level implementation effects and will need to be interpreted in the context of implementation analysis findings.

Multiple imputation using chained equations will be used for missing data under a range of scenarios from missing at random to informative missingness. Sensitivity of parameter estimates to these assumptions will be evaluated.

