## 9.3 Exploratory Objectives

Heterogeneity of cancer diagnoses for patients in the NU IMPACT trial makes formal analysis of clinical outcomes a challenge. However, we will undertake exploratory analyses of clinical outcomes to assess differences in the Pre-I, Post-I UC and Post-I EC arms. Clinical endpoints to be ascertained via the electronic medical record through 12 months of follow-up include the following for each cancer continuum cluster: curative intent – recurrence, secondary cancers, disease-free and overall survival; non-curative intent – secondary cancers, progression-free and overall survival; survivorship – recurrence. Kaplan-Meier curves will be used to estimate distributions for time-to-event outcomes disease-free, progression-free and overall survival within treatment arm, and global differences across arms will be compared using logrank tests. Cox proportional hazards regression models will be used to estimate hazard ratios, treating the Pre-I cohort as the referent. Frequencies of binary outcomes recurrence and secondary cancers will be summarized across treatment arms

and compared using chi-square tests. Logistic regression models will be used to estimate odds ratios, treating the UC cohort as the referent with global and pairwise comparisons for Post-I EC v. Post-I UC and Pre-I v. Post-I UC. Regression models will be adjusted for cluster, cancer continuum, gender, language preference, and time of enrollment. If differences in demographic or baseline variables are detected across treatment arms, we will evaluate sensitivity of estimated hazard and odds ratios to further adjustment for these variables. Importantly, given the heterogeneity of outcome rates for different cancers, we will conduct these analyses separately for each type of cancer diagnosis. Given the subset nature of these investigations, these analyses will be considered exploratory.

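### SAP 9.1 codes Pre-I as one fixed group, but most Pre-I follow-up falls after the patient's own cluster has crossed over, which dilutes the UC v. Pre-I contamination check

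*Combined protocol and SAP*

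**What the plan says.** SAP 3.0 (Effectiveness Study) sets the Pre-I schedule: "For the last 6 months of each cluster's pre-I phase, eligible participants are invited to consent to monthly administration" of the surveys, which are "administered through REDCap for one year following consent". SAP 2.0 gives the primary outcomes as "Individual-level PROMIS measures collected at baseline and monthly up until 12 months after enrollment". In Figure 2, each cluster's "Pre-I: Follow-up Only" bar starts in the quarter in which that cluster's randomised recruitment starts. Pre-I patients stay in care at these clinics but cannot receive EC. SAP 3.0 (Implementation Study) says that most implementation strategies start at, or just before, the cluster's transition.

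SAP 3.0 describes the Pre-I v. UC comparison as critical for noticing contamination of provider care after the system-wide strategies begin. SAP 9.1 carries it out by "extending the primary predictor of interest to a multicategory variable (Post-I EC, Post-I UC, Pre-I"), adjusting for quarter of enrolment among other covariates. The decision rule begins "If longitudinal PROs for Post-I UC and Pre-I are not significantly different". If, in addition, EC v. Pre-I resembles EC v. UC, the SAP takes this to suggest that contamination is absent. Section 9.1 has no indicator of crossover at the time of assessment, no cut-off of Pre-I data at crossover, and no margin.

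**The concern.** A contamination check of this kind needs a comparator that has largely escaped the exposure. Here the Pre-I patient is treated, for most of the follow-up year, by the same clinicians working under the same implementation package as the UC patient. If the package changes provider behaviour, both sides of the contrast move and the difference shrinks.

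The covariate for quarter of enrolment does not help, because the exposure changes during a patient's follow-up. The rule then reads a small, non-significant difference as reassurance. The SAP's caveat about system-level effects applies only when a difference is found. The trial could therefore report that contamination was absent on the strength of a check with little ability to detect the kind that SAP 3.0 says it is for.

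**Working it through.** **1. The SAP's own sample size, to fix the variance model (SAP 6.0).** Inputs: 0.3 SD, alpha 0.01 (taken as two-sided), 90% power, compound symmetry with correlation 0.5. The variance factor for the mean of 12 follow-up assessments is (1 + 11 × 0.5)/12 = 0.5417. Per arm, n = 2 × 0.5417 × (2.576 + 1.282)²/0.3² = 179.1, so 180, or 360 in total. Then 360/(1 − 0.64) = 1000. Both SAP figures reproduce.

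**2. Share of Pre-I assessments after crossover.** Assume enrolment is uniform over the 6 months before crossover. Assessment k then falls after crossover with probability min(k/6, 1). Summed over months 1-12 this is 3.5 + 6 = 9.5, and 9.5/12 = 79.2%. The earliest enrollee has at least 50% of assessments after crossover and the latest has 100%. On average 2.5 assessments per patient precede crossover, all in months 1-5.

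Other assumptions:
- person-time instead of assessments: 9/12 = 75%
- counting baseline: 9.5/13 = 73.1%
- linear dropout reaching 64% at month 12 (SAP 6.0): 72.1%
- nine-month enrolment (Protocol 4.0): 8/12 = 66.7%
- nine-month enrolment with 64% dropout: 58.0%
- everyone enrolled in the first 1-2 months of the 6-month window: 7/12 to 7.5/12, or 58-63%

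**3. Dilution.** For an immediate effect reaching every patient in the clinic, UC is exposed at 100% of assessments and Pre-I at 79.2%, so the contrast keeps 20.8%. At a 58% share it keeps about 42%. For an effect that builds linearly after crossover, with UC enrolment uniform over the 6 months after crossover, mean exposure is:

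| Build-up | UC | Pre-I | Kept, (UC − Pre-I)/UC |
|---|---|---|---|
| 3 months | 0.988 | 0.667 | 33% |
| 6 months | 0.936 | 0.542 | 42% |
| 12 months | 0.739 | 0.323 | 56% |
| 18 months | 0.528 | 0.216 | 59% |

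**4. Power of UC v. Pre-I, two-sided 5%.** The UC arm is 500 (half of 1000). The SAP gives no Pre-I target, so 500 is an assumption; attrition is ignored. Unadjusted SE = √(2 × 0.5417/500) = 0.0465. SAP 9.1 adjusts for baseline; if the 0.5 correlation extends to baseline, the variance factor is 0.5417 − 0.25 = 0.2917 and SE = 0.0342.

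| Immediate 0.15 SD effect | Contrast (SD) | Unadjusted | Baseline-adjusted |
|---|---|---|---|
| Clean comparator | 0.15 | 90% | 99% |
| 79% post-crossover | 0.031 | 10% | 15% |
| 58% post-crossover | 0.0625 | 27% | 45% |

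An immediate 0.30 SD effect at the 79% share also gives a contrast of 0.0625 SD (27% unadjusted). A 12-month build-up to 0.30 SD gives about 0.12 SD and about 76% unadjusted.

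Group size matters. With 500 v. the 6,336 Pre-I patients in Protocol 4.0, unadjusted power at the 79% share is 15% for 0.15 SD and 45% for 0.30 SD. With that protocol's 3,168 v. 6,336 it is 50% and 97%.

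**5. The decision rule.** Within the three-group model, (EC − Pre-I) − (EC − UC) = UC − Pre-I. The second condition therefore restates the first. Even without dilution, a true 0.1 SD difference would be non-significant 75% of the time at 180 per group (58% baseline-adjusted) and 43% at 500 per group (17% baseline-adjusted).

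**6. Section 9.2.** Under the same uniform assumption, 3/6 = 50% of Pre-I person-time to month 6 and 9/12 = 75% to month 12 is post-crossover.

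**The case against.** A reader might infer that the check would report no contamination whatever had happened. The documents do not support that. The contrast is attenuated, not removed, and at the protocol's cohort sizes a diluted immediate 0.30 SD effect would usually be found. Section 9.1 also speaks of contamination between treatment arms. EC material passed only to randomised UC patients never reaches Pre-I patients and is not diluted in this way. SAP 3.0 does, however, name provider care as the target, and that route is the diluted one.

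A reader might also take 79% as a fixed property of the design. It rests on uniform enrolment and no dropout. Anyone seen in the past year is eligible (SAP 4.0) and patients are flagged by nightly data pulls (Protocol 10.0), so enrolment could be front-loaded. The share then falls to about 58-63%, which is still most of the follow-up.

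Section 9.1 says that the added data come from the Pre-I period, which could mean pre-crossover assessments only. Elsewhere 9.1 and SAP 3.0 speak of Pre-I patients and of patients enrolled during pre-I, which favours the reading used here. On the other reading, a 12-month UC average would be set against about 2.5 early assessments per Pre-I patient, so 9.1 would still need rewording.

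Finally, it is tempting to call the Cox model in 9.3 wrong for "treating the Pre-I cohort as the referent". In a three-group model the referent only reparametrises, and EC v. UC remains available as a contrast. The analysis is exploratory and sets out to compare all three groups.

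**Conclusion.** The concern holds for contamination that acts through providers or the system from crossover onwards. Most Pre-I follow-up is post-crossover under every assumption tried (about 58-79%). The UC v. Pre-I contrast keeps about 21% of an immediate clinic-wide effect at the 79% share, and about 33-59% of one that builds over 3 to 18 months. The power figures depend on an assumed Pre-I size and on whether the baseline correlation is 0.5. Together with a rule that treats non-significance as evidence of absence, the check leans towards reassurance.

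It does not follow that the primary result is biased by this coding: that estimate compares EC with UC on randomised post-I data and does not use Pre-I. The Pre-I model is a supporting analysis with hedged wording. For that reason this is a should-fix and not a threat to the main conclusion.

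**What to change.** In SAP 9.1:
- State which Pre-I assessments enter the model.
- Add a time-varying indicator of own-cluster crossover at each assessment, so that Pre-I data before and after crossover are separate levels. Compare the pre-crossover level with UC at matched follow-up months.
- Report UC v. Pre-I with its confidence interval and do not conclude absence of contamination from non-significance. Call the result inconclusive when the interval includes differences that matter relative to the planned 0.3 SD, using a margin that the sponsor justifies.
- Drop the second condition as a separate check, or say that it restates the first.

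The documents give no basis for a particular margin, and a tight one may be out of reach. At 180 per group with all 12 months used, the 95% half-width is 1.96 × √(2 × 0.5417/180) = 0.15 SD unadjusted, or 1.96 × √(2 × 0.2917/180) = 0.11 SD baseline-adjusted, so a margin of 0.1 SD could not be met.

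In 9.2, note or account for the same post-crossover exposure. Making UC the Cox referent in 9.3 is an optional consistency change.

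The cost is SAP wording, which by SAP 1.0 needs no protocol amendment; the crossover schedule and survey timing are already part of the study's data. The price is precision: the clean contrast covers only about months 1-5, rests on about 2.5 Pre-I assessments per patient, and will often be inconclusive.
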